### Analyses

Data will be analyzed according to intention-to-treat principles. Data will be checked for completeness and the characteristics and frequency of missing data will be described. Missing data values will be imputed as appropriate.

Our primary hypothesis is that patients in the SRA+G arm will have a greater reduction in insulin resistance and lose a greater percentage of their baseline weight after 12 months compared to patients in the SRA arm. We will test these hypotheses with linear multiple regression models with weight or insulin resistance at 12 months as the outcomes (testing a separate model for each outcome) and arm, clinic site, and baseline patient characteristics as explanatory and control variables. We will test our hypothesized mechanism with mediation analysis; specifically, hierarchical linear regression models will test whether effects of the intervention on insulin resistance and weight at 12 months is partially or fully accounted for by perceived risk at 3 months.

Our secondary hypotheses are that patients in the SRA+G group will report significantly healthier dietary changes and will have significantly greater average weekly energy expenditure than patients in the SRA group after 3 months. We will test this hypothesis with linear multiple regression models with behavioral variables at 3 months as the outcomes (testing a separate model for each variable) and arm, clinic site, and baseline patient characteristics as explanatory and control variables. We predict that this difference will narrow, but will still be significant at 12 months; we will test this hypothesis by fitting the same regression model with 12-month behavioral variables as outcomes. In addition, we hypothesize that overweight and obese patients in the SRA+G group, irrespective of diabetes genetic panel test result, will have a greater reduction in waist circumference. Residualized change scores (controlling for baseline values) will be used for 3- and 12-month outcome variables.

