### Power and sample size considerations

Power and sample size estimates are based on the primary study outcomes, percent weight change (from baseline) and change in HOMA-IR, both after 12 months. Based on two studies of low-intensity clinic-based weight loss interventions, we estimate that approximately 20% of patients in the SRA+G arm will lose 5% of their body weight over the course of a year, compared to approximately 10% of patients in the SRA arm [36,37]. Under these assumptions, the mean weight change for participants in the SRA+G arm is estimated to be around 1.7% of baseline body weight, with a standard deviation of approximately 3.9; and the mean weight change to be zero in the SRA arm. We further assume that changes in weight follow normal distributions with equal standard deviations for both groups. Because we are studying a low-intensity informational intervention, for purposes of sample size calculation we will aim for sufficient power to detect a difference in weight change that is 2/3 of the 1.7% difference estimated above. Thus, approximately 198 patients are needed in each group for a two-sided type I error rate of 0.05 and 80% power.

From a number of comparable studies, we conservatively estimate that participants in the SRA+G arm will be able to lower HOMA-IR by 0.5 over the course of a year through lifestyle changes; those in the SRA arm are again assumed to have a mean change of zero. Mean baseline HOMA-IR is estimated to be 2.5 with a standard deviation near 2.0 [38-41]. Using these estimates, 253 patients per group would be required to achieve a significance level of 0.05 with 80% power.

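### The 12-month regression named as the test tests whether the behavioural arm difference persists, but not whether it has narrowed since 3 months

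*Protocol article*

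**What the plan says.** All of this stands in the Analyses section of the protocol article.

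- **3-month hypothesis.** SRA+G patients "will report significantly healthier dietary changes and will have significantly greater average weekly energy expenditure than patients in the SRA group after 3 months". It is tested by a separate linear regression for each behavioural variable, with "arm, clinic site, and baseline patient characteristics as explanatory and control variables".
- **12-month hypothesis.** "We predict that this difference will narrow, but will still be significant at 12 months". This has two parts: the arm difference gets smaller, and it is still detectable.
- **Named test.** "we will test this hypothesis by fitting the same regression model with 12-month behavioral variables as outcomes".
- **Outcome scale.** "Residualized change scores (controlling for baseline values) will be used for 3- and 12-month outcome variables".

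No repeated-measures model, arm-by-time term or contrast between the 3- and 12-month arm effects appears in Study measures: Outcomes, Process Measures, Analyses or Power and sample size considerations. The last moderation hypothesis in Analyses concerns maintenance of behaviour at 12 months. It relates maintenance to perceived control over risk, not to a change in the difference between arms.

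**The concern.** Narrowing is a statement about the arm effect at 3 months minus the arm effect at 12 months. The named model estimates only the second of these. It contains no 3-month value, time term or arm-by-time term, and residualizing on baseline does not bring the 3-month value in. One half of the stated hypothesis therefore has a test assigned to it that cannot answer it.

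What is at stake is the interpretation of durability. The Conceptual framework section suggests that genetic risk information may act as a lasting reminder of threat. Any later statement that the behavioural effect faded or held up should rest on an estimate of change with its uncertainty, and the plan provides none.

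**Working it through.** **Step 1. Match each part of the prediction to the model.** Let b3 and b12 be the arm coefficients from the 3- and 12-month models.

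| Part of the prediction | Quantity needed | Given by the named model? |
|---|---|---|
| Still significant at 12 months | b12 and its SE | Yes |
| Will narrow | b3 − b12 and its SE | No |

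The variance needed is Var(b3 − b12) = Var(b3) + Var(b12) − 2 Cov(b3, b12). Two separate regressions give the first two terms. The covariance is not zero, because the same patients contribute to both, and neither model estimates it.

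The mismatch is complete at this step. The remaining steps only illustrate its size.

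**Step 2. Inputs for the illustration.** The article gives no effect size, SD or correlation for diet or energy expenditure, so there is no plan figure on this point to reproduce. I borrow 253 per arm from the HOMA-IR calculation in Power and sample size considerations ("253 patients per group would be required to achieve a significance level of 0.05 with 80% power"). That figure does reproduce. With effect 0.5 and SD 2.0, n = 2 × (1.96 + 0.842)² / (0.5/2.0)² = 2 × 7.85 / 0.0625 ≈ 251.2, so 252 per arm by the normal approximation and 253 by the t distribution. Its use for the behavioural outcomes is an assumption, as are outcome SD 1 at both times and the effects and correlations below.

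**Step 3. Does the 12-month result carry information about narrowing?** Simulation of 4,000 trials per row, baseline-adjusted, with all correlations among baseline, 3 and 12 months equal to 0.5:

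| True 3-month effect (SD) | True 12-month effect (SD) | Truth | 12-month model significant | Direct contrast significant |
|---|---|---|---|---|
| 0.50 | 0.25 | halved | 0.903 | 0.79 |
| 0.25 | 0.25 | unchanged | 0.907 | 0.043 |
| 0.125 | 0.25 | doubled | 0.894 | 0.28 (widening) |

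The simulated 12-month data do not depend on the 3-month effect, so the small differences in the fourth column are simulation error. The 12-month result is the same whichever row is true. Only the direct contrast separates them.

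**Step 4. What the direct contrast can deliver.** With r the correlation between 3 and 12 months, SE = √(2(1 − r)) × √(2/253), where √(2/253) = 0.0889. Power for a true narrowing of 0.1 SD is Φ(0.1/SE − 1.96) + Φ(−0.1/SE − 1.96).

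| r | SE | 95% CI half-width (1.96 × SE) | Power for 0.1 SD |
|---|---|---|---|
| 0.3 | 0.105 | 0.21 SD | 16% |
| 0.5 | 0.089 | 0.17 SD | 20% |
| 0.7 | 0.069 | 0.13 SD | 31% |

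Over the same range of r, halving a 3-month effect of 0.25 SD gives power of 22–44%, and halving one of 0.5 SD gives 66–95%.

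**The case against.** **Persistence is the real claim.** It can be argued that narrowing is only a concession that the effect will weaken, and that persistence at 12 months is what the authors want to infer. On that reading the fault is one loose phrase. This has some force: the persistence half is correctly tested, and a reader should not infer that the whole 12-month hypothesis is untested. But the article calls the two-part prediction a hypothesis and names its test, so this is not a detail left to a fuller document.

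**False claims of narrowing.** A reader might infer that the plan would often yield them. With equal true effects of 0.25 SD at both times, both models are significant with a smaller 12-month estimate in about 34–36% of trials (correlation 0.3–0.7). The documents do not support using this as an error rate. They set no rule for declaring narrowing and nowhere say that the two estimates or p-values will be compared. The figure also follows the assumed effect: 3–6% at 0.1 SD and about 49% at 0.4 SD. A further 9–13% of trials at 0.25 SD are significant at 3 months but not at 12, which would contradict the article's prediction rather than support it.

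**Drop-out.** A reader might also infer that the two models use different patients, so that losses alone could look like narrowing. The Analyses section commits to intention-to-treat and to imputation where appropriate, and the article gives no attrition figure. Differing patient sets are possible but not established.

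**Low power.** A direct test may often be inconclusive, as step 4 shows. This stands. It is a reason to report the interval, or to call narrowing descriptive, but it does not make the 12-month model a test of narrowing.

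**Conclusion.** The point holds for the narrowing clause alone. The named 12-month regression is a sound test of whether the arms differ at 12 months and gives no information on whether the difference has changed since 3 months. This follows from the model's content and needs no numerical assumption. The simulation and power figures are illustrations that rest on 253 per arm, SD 1 and the stated effects and correlations, none of which the article gives for diet or energy expenditure.

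Priority is low. One clause of a secondary, self-reported behavioural hypothesis is affected. The primary outcomes, the sample size and the arm comparisons at 3 and 12 months are untouched.

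**What to change.** Keep the 3- and 12-month models for the arm differences. For diet and energy expenditure, add one direct estimate, with 95% CI, of the change in the arm effect, by either route:

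- the arm-by-time contrast from one baseline-adjusted repeated-measures model of the 3- and 12-month values, with within-patient correlation; or
- a regression of each patient's 3-minus-12-month difference on arm with the same covariates. If the residualized scores are kept and the same patients enter throughout, least squares makes this estimate exactly b3 − b12.

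Alternatively, reword the section so that narrowing is a descriptive expectation that is not tested, and tie the 12-month model to persistence only.

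The cost is a wording change and at most one extra model for each of the two behavioural outcomes, using data already planned for collection. Because power is modest, the contrast should be read from its interval, and a non-significant result should not be taken as evidence that the effect was maintained.

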### Power and sample size considerations

Power and sample size estimates are based on the primary study outcomes, percent weight change (from baseline) and change in HOMA-IR, both after 12 months. Based on two studies of low-intensity clinic-based weight loss interventions, we estimate that approximately 20% of patients in the SRA+G arm will lose 5% of their body weight over the course of a year, compared to approximately 10% of patients in the SRA arm [36,37]. Under these assumptions, the mean weight change for participants in the SRA+G arm is estimated to be around 1.7% of baseline body weight, with a standard deviation of approximately 3.9; and the mean weight change to be zero in the SRA arm. We further assume that changes in weight follow normal distributions with equal standard deviations for both groups. Because we are studying a low-intensity informational intervention, for purposes of sample size calculation we will aim for sufficient power to detect a difference in weight change that is 2/3 of the 1.7% difference estimated above. Thus, approximately 198 patients are needed in each group for a two-sided type I error rate of 0.05 and 80% power.

From a number of comparable studies, we conservatively estimate that participants in the SRA+G arm will be able to lower HOMA-IR by 0.5 over the course of a year through lifestyle changes; those in the SRA arm are again assumed to have a mean change of zero. Mean baseline HOMA-IR is estimated to be 2.5 with a standard deviation near 2.0 [38-41]. Using these estimates, 253 patients per group would be required to achieve a significance level of 0.05 with 80% power.

## Discussion

An important gap suggested by AHRQ-EPC [42] and USPSTF [43] reviews is the relative lack of effective strategies for increasing patients' motivation for and adherence to lifestyle changes known to reduce risk for type 2 diabetes. The study described herein examines a novel alternative strategy, in which patients are counseled about their germline genetic risk for type 2 diabetes as part of a comprehensive risk assessment. To our knowledge this is the first RCT to assess the *clinical utility *of disclosing the results of DNA testing for common variants associated with increased risk for type 2 diabetes. Study outcomes include patients' emotional and behavioral responses to this additional information, behavior changes (if any), and clinical endpoints. In addition, this study also addresses the *personal utility *of DNA testing. Our hypothesized mechanism of effect is that provision of type 2 diabetes genetic risk information during the risk counseling intervention will alter perceived risk, which will in turn increase motivation to engage in preventative health behaviors. Personal utility captures potential benefits of DNA testing that cannot necessarily be directly quantified in clinical outcomes [44].

Because this is one of the first trials to test for behavioral and clinical effects of communicating genetic test results, we carefully considered several novel and important issues during its development and design.

### Ethics of Communicating Genetic Risk Information

Adding genetic testing to standard risk assessment provides little improvement in the degree of absolute prediction of risk for developing type 2 diabetes. In designing the risk profile, we aimed to facilitate framing and evaluation of individual risk through suggestions of magnitude and meaning of results, and also to avoid falsely reassuring or overly alarming messages. By abstaining from presenting normative statements regarding the degree of genetic risk, we sought to keep participants from developing notions of fatalism or false security that might undermine motivation to change behavior [39].

### Strategy for Risk Communication

We aimed to simplify the presentation of risk information to be complete yet readily understood by patients. To this end, our risk profile (1) placed genetic risk information in context alongside other major risk factors for type 2 diabetes, (2) did not require a sophisticated understanding of either genetics or statistics, and (3) communicated personalized, evidence-based messages regarding individual risk which could then be further explained and amplified during the risk counseling visit (see Figure 2). This profile can readily be expanded to incorporate additional genetic risk markers for type 2 diabetes; and could even be adapted for use in other chronic diseases (e.g., coronary heart disease).

Combining different categories of risk information represented a particular challenge, especially given that patients' understanding and evaluation of their various risks are highly individualized. While the *magnitude *of risk may be a computable, objective quantity, the *meaning *of that risk for the individual is subjective and qualitative, and affected by many factors [45]. Genetic epidemiology has thus far almost exclusively focused on quantitative precision, and as a result, probably overemphasizes the significance of exactness when informing individual patients of their risks for a chronic disease. With this in mind, our risk profile was based on prospect theory, an established framework for understanding risk assessment and decision-making that has been previously applied to framing risk messages to promote healthy behavior [46,47]. Prospect theory posits two phases: editing (or framing) and evaluation; our risk profile was designed to address both.

The editing (or framing) stage is where the decision-maker's reference point is determined. We chose not to frame patients' risk information as a single quantity (i.e., "You have *x*% risk of getting diabetes in the next *y *years") for two reasons: First, there does not yet exist a comprehensive (prospective) risk prediction tool that combines and quantifies all of the known risk factors for type 2 diabetes, even excluding genomic risk. Second, individual differences in numeracy would likely have resulted in variation in understanding such a quantity [48]. Instead, we chose to simultaneously present patients with a number of distinct factors contributing to their overall risk for type 2 diabetes in relatively simple terms. Patients can evaluate each contributing risk factor in its own right, and each individual can arrive at an overall gestalt rather than having to interpret an abstract quantity.

Patients' valuing and weighting the overall risk for type 2 diabetes as a product of accepted, understood risk factors is described by prospect theory's evaluation phase. In our risk profile, different suggestive colors are used to highlight different degrees of risk for each factor. Simple quantitative reports and explanations are used to report blood sugar, number of relatives with type 2 diabetes, number of higher-risk alleles, and other risk factors (this "semi-quantitative" approach is based on the finding that individuals tend to gauge risk relative to other individuals or other risks [49]).

### Strengths of the Study

First, to increase the potential generalizability of the study to other primary care settings, we made the deliberate decision to use embedded clinicians already practicing at each clinic site to provide risk counseling, rather than inserting study personnel or referring study participants to outside genetic counselors. Second, to increase the potential for replication of any findings, we chose not to implement a supplementary behavioral intervention along with risk counseling. Although such a behavioral intervention might increase the effectiveness of risk counseling for increasing preventive behaviors, it also might have the effect of complicating the identification of unique effects of genetic testing. In addition, in many primary care settings, a discrete behavioral intervention may not be feasible due to cost and other resource constraints. Third, our risk counseling protocol is theory-based and relatively simple, maximizing the possibility that should the intervention prove successful, it might be more readily replicated in other settings with few additional resources required. In summary, although the main outcome measures are designed to test the effects of genetic risk information on clinical and behavioral outcomes related to prevention of a particular chronic disease (i.e., type 2 diabetes), results from this study could also inform the future development and implementation of care models for the use of individual genetic risk information in primary care more generally.

### Conclusion

The clinical and personal utility, feasibility, and efficacy of providing patients with genetic risk information for common chronic diseases in primary care remain largely unknown. The novel study described here aims to address these knowledge gaps, and the findings will contribute to the evidence base regarding the use of genetic risk testing to promote behaviors that reduce the risk of type 2 diabetes and other diseases. In addition, study design features such as employing existing clinic personnel for risk counseling and the creation of a comprehensive risk communication tool that includes both genetic and non-genetic factors, could be adapted for other settings and chronic conditions of interest, informing the future development and implementation of care models for the use of individual genetic risk information in primary care.

## Abbreviations

AHRQ-EPC: Agency for Healthcare Research and Quality-Evidence-based Practice Centers; BMI: body mass index; DNA: deoxyribonucleic acid; DPP: Diabetes Prevention Program; GWAS: genome-wide association study; HOMA-IR: HOmeostasis Model Assessment of Insulin Resistance; RCT: randomized controlled trial; SNP: single nucleotide polymorphism; SRA: standard risk assessment; SRA+G: standard risk assessment + upfront disclosure of genetic risk testing results (i.e., the SRA+G arm); USPSTF: United States Preventive Services Task Force.
